#### Study Governance

A project management group comprising the chief investigator, coinvestigators (including patient and public involvement [PPI] coinvestigators), an external researcher, and additional PPI representatives from the Community for Research Involvement and Support by People With Parkinson Diseases (King’s College London) will review progress to provide study governance and oversight and to ensure there are no ethical concerns with the study. Planned deviations or waivers to the protocol are not allowed under the UK regulations on clinical trials and will not be used.

### Safety Considerations

A comprehensive risk register and hazard log has been maintained for NMS Assist across its development as part of its clinical safety management file. This risk register will be regularly reviewed and updated as part of the project management governance. Key risks for this project include the following:

Clinical: people with Parkinson disease, care partners, or HCPs are unwilling to incorporate the system into routine use; mitigated by a prior extensive cocreation process focused on user-centered designExcessive screen time: health risks associated with excessive screen time are mitigated encouraging users to complete the strategies and skills taught by the app away from the screen. All risks and mitigations are outlined in the clinical safety management fileTechnical: the system provides inappropriate decision support for clinicians; mitigated by supervision by the clinical research team, review of any errors, and extensive safety evaluation

## Results

The study was awarded funding for 24 months in August 2021. Data collection is expected to begin in December 2022 and the study is expected to be completed by March 2024.

## Discussion

### Anticipated Findings

The evaluation is expected to show that the NMS Assist system has a positive impact on patient and care partner knowledge, skills, and confidence at managing NMS and general well-being. In addition, the results are expected to demonstrate the acceptability and accessibility of the system for users and its feasibility for implementation within NHS services.

### Strengths and Limitations

A key strength of the intervention and study protocol is their co-design and development with PPI coinvestigators. The full execution of the study will be conducted in collaboration with PPI coinvestigators and other PPI representatives. Another strength is that the study has a long follow-up period (12 months) over which participants can use the NMS Assist system, which will enable an examination of the sustainability of the system’s adoption in clinical and home settings.

A limitation of the study is its ability to assess the health and well-being outcomes measured. The study design does not enable a comparison between groups, which would provide stronger evidence of the system’s potential impact. The generalizability of the results is also limited by the system, which requires that participants own a compatible device and be fluent in English.

### Dissemination Plan

Analysis of the data will be compiled into a published peer-reviewed paper. People with Parkinson disease, care partners, and HCP investigators involved in the project will be integral in disseminating the results. PPI representatives will help develop and edit communications for all audiences, but, in particular, the summary of results that will be sent to all study participants. They will take the lead in disseminating and presenting results to the broader Parkinson community and professional groups such as through patient networks, the Parkinson’s UK research network, patient and care partner congresses and conferences and the World Parkinson’s Congress (which includes patients and professionals), newsletters, articles, and social media. Academic members of the project team will disseminate the results through peer-reviewed journal publications and at research conferences.

The newest version of NMS Assist will be made publicly available to people with Parkinson disease and care partners after the system refinement stage (6 months after project commencement). This access will be available concurrent to our study, and members of the public will have the ability to consent into the study if they choose. We will make the data collected by NMS Assist freely accessible for research purposes by creating a data set that can be stored and shared securely in a data safe haven. To ensure that this data asset is used most appropriately, we will consult with Parkinson’s UK and other stakeholders when developing our data sharing policy. In future, this will enable us to provide free and secure access to the data for people who apply to use it for research purposes, while accounting for data security and ethical considerations.

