### Sample Selection and Recruitment

People with Parkinson disease attending outpatient clinics through the University Hospitals Plymouth NHS Trust Parkinson service are eligible for this study (see Textbox 1 for eligibility criteria). All people with Parkinson disease and care partners who are willing and eligible will be included, with the intention of recruiting a representative sample based on various demographic and Parkinson-specific characteristics. The participants invited to the semistructured interview will be randomly selected from within different demographic and disease characteristic categories; we will continue recruitment in the semistructured interviews until we have reached demographic saturation to ensure we complete in-depth qualitative understanding of the impact of the system.

Recruitment will take place through the Plymouth Parkinson service. People with Parkinson disease attending outpatient clinics at the Plymouth Parkinson service will be invited to participate in the study along with their care partner. The associated HCPs responsible for the care of people with Parkinson disease and care partner dyads who consent into the study will then be invited to participate as well. Patients will be recruited during clinical appointments with the Plymouth Parkinson service by research nurses who will provide them with a paper participant information sheet to consider and will collect verbal or written consent using a preestablished informed consent form. Associated HCPs of the people with Parkinson disease who consent into the study will be invited to participate in the study for use of the clinician portal (and provided with an HCP version of the participant information sheet and informed consent form).

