### Study Duration and Follow-up

The study will consist of 3 main phases over 24 months: preparation (6 months), delivery of the intervention (12 months, see Figure 1 for follow-up data collection points), and analysis and dissemination (6 months). The study team will monitor the use of NMS Assist and assure the system is being used within designed parameters during the study. No incentives will be provided to encourage adherence; the study is assessing the use of NMS Assist in the real world, and we expect that the benefits for people with Parkinson disease and care partners provided by the monitoring and self-help features will sufficiently encourage adherence to the study.

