#### Recruitment

Participant eligibility will be determined by the screening process they undergo in outpatient care at the University Hospitals Plymouth NHS Trust. All eligible participants will be invited to participate with no influence from the researchers. Interview participants will also be randomly selected (from demographic groups) by a computer script of intervention users. All participants will be included in the process evaluation’s quantitative analyses, thus avoiding recruitment bias.

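### The Dissemination Plan opens the study to members of the public, against the clinic-only entry rules, and no criterion excludes people who have already used the released app

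*Protocol article*

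**What the plan says.** **Who may enter.** Sample Selection and Recruitment states that "People with Parkinson disease attending outpatient clinics through the University Hospitals Plymouth NHS Trust Parkinson service are eligible for this study" and that "Recruitment will take place through the Plymouth Parkinson service", with research nurses approaching patients at appointments. Textbox 1 requires that the patient is normally under that service and that the patient's own health care professional there has consented. The Recruitment paragraph under Ethical Considerations adds that "Participant eligibility will be determined by the screening process they undergo in outpatient care at the University Hospitals Plymouth NHS Trust".

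**Public release.** The Dissemination Plan makes the newest version public "after the system refinement stage (6 months after project commencement"). The release overlaps with the evaluation: "This access will be available concurrent to our study". The same sentence then gives public users a way in, because it says that "members of the public will have the ability to consent into the study if they choose". Data sharing is dealt with in the sentences that follow, as a separate matter.

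**Prior exposure.** Textbox 1 excludes people who were involved in developing or testing the system. It does not mention people who have simply used it.

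**Baseline and analysis.** Quantitative Data Collection places the first activation score at the start of the intervention period, with monthly scores after that. Data Analysis compares mean scores over 13 time points in one group. Strengths and Limitations acknowledges that there is no between-group comparison.

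**The concern.** There are two linked problems.

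The first is a conflict about the study population. The Methods describe a closed, clinic-based cohort at one NHS Trust. The Dissemination Plan describes a second way in, for the general public, with no condition attached. A person outside the Plymouth service cannot satisfy the two service-related inclusion criteria and would not pass through the stated recruitment and screening route. Nothing says whether such a person counts towards the 60 dyads, or enters the denominators for retention, engagement and health care contacts. In a feasibility study those are main results.

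The second is the baseline. With no control group, the baseline score is all that later scores can be judged against. If some participants have used the app before they give it, part of any change has already happened, and the later scores are compared with the wrong starting point. An observed positive effect on activation is one of the success criteria in the abstract, so this reference point matters to the study's own decision. A baseline missed before first use cannot be recovered afterwards.

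**Working it through.** The plan gives no effect size, standard deviation or power, and the 60 dyads rest on achievability, so there is no stated figure to reproduce. The check sets the sections side by side and works through the timeline.

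**Entry rules compared**

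| Requirement | Methods, Textbox 1 and Recruitment | Dissemination Plan |
|---|---|---|
| Under the Plymouth service | Required | Not mentioned |
| Own health care professional consented | Required | Not mentioned |
| Recruited at a clinic appointment | Yes | Own choice to consent in |
| Screened in Trust outpatient care | Yes | Not mentioned |
| Separate cohort | None described | None described |
| Earlier ordinary use of the app | Not excluded | Made possible by the release |

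**Timeline**

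1. Study Duration and Follow-up gives "preparation (6 months), delivery of the intervention (12 months, see Figure 1 for follow-up data collection points"), followed by 6 months of analysis and dissemination. Delivery therefore runs from month 6 to month 6 + 12 = 18.
2. Public release is at month 6, so the public version is available throughout delivery.
3. Results states: "The study was awarded funding for 24 months in August 2021. Data collection is expected to begin in December 2022". August 2021 to December 2022 is 16 months. The article does not date project commencement, so two readings follow.
   - *Assumption A: the project starts at the award.* Release falls at August 2021 + 6 months = February 2022, which is 16 − 6 = 10 months before the first baseline.
   - *Assumption B: the project starts 6 months before data collection, about June 2022.* Release and first baseline coincide in December 2022. Only people enrolled later could have used the public version first.
4. Results expects completion by March 2024, which is 15 months after December 2022. If each participant is followed for 12 months, enrolment can stretch over at most about 15 − 12 = 3 months. Under B, prior public access before baseline is then between 0 and about 3 months. Under A it is between 10 and about 13 months.

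**What exposure before baseline would do**

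Let *f* be the share of participants with prior use and *g* the share of their gain already realised at baseline. If nothing else differs between them and the rest, observed mean change = (1 − *f* × *g*) × true mean change. The documents give neither quantity. For assumed values only:

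| *f* (of 60) | *g* = 0.5 | *g* = 1 |
|---|---|---|
| 10% (6) | 1 − 0.05 = 95% | 1 − 0.10 = 90% |
| 25% (15) | 1 − 0.125 = 87.5% | 1 − 0.25 = 75% |
| 50% (30) | 1 − 0.25 = 75% | 1 − 0.50 = 50% |

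The table shows the mechanism and is not an estimate. People who seek out the app may also be more motivated and change more, which would push the other way.

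**The case against.** The strongest reply is that the Dissemination Plan does not say the criteria are relaxed. Sample Selection and Recruitment takes in people who are both willing and eligible, and Study Governance rules out planned deviations and waivers. Read together, a member of the public who consents must still meet Textbox 1. Such a person would then have a consented professional and attend the three visits like anyone else. A Plymouth patient who downloads the app is also a member of the public. This largely stands: a reader might infer that ineligible people will be enrolled, without clinicians or visit data, but the text does not support that. What survives is the conflict over the route of entry, and wording that leaves the analysis population undefined.

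A second reply is that exposure before baseline is hypothetical. Under assumption B, people enrolled at the start of delivery have had no public access, and the article gives no enrolment schedule. This also stands in part. A reader might infer that such baselines will occur; the documents show only that nothing prevents them. The gap also remains if public entrants are held to Textbox 1, because an eligible Plymouth patient may use the released app before being approached in clinic.

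A third reply is that this is a feasibility study that disclaims measuring efficacy, already admits the lack of a comparator and aims at real-world use. That limits the consequences. It does not remove the conflict, since adoption and retention also depend on who counts as a participant.

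Finally, an article condenses its protocol, and checks for earlier use might sit in the full document. That answers a complaint about missing detail. It does not answer two printed statements about entry that disagree.

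**Conclusion.** The point holds in two parts, with different strength.

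The conflict between the Dissemination Plan and the recruitment, eligibility and screening text is plain on the page and rests on no assumption. As written, the plan does not settle whether public entrants belong to the 60-dyad evaluation.

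The risk of a baseline taken after exposure is a sound inference from three facts: release no later than the start of delivery on the plan's own phases, an exclusion limited to development and testing, and no rule tying the first activation score to first use. How much prior access is possible depends on the undated project start, from none to about 3 months on one reading and 10 to about 13 on the other.

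No percentage loss of effect should be attached to this. The share of prior users, the gain they would bring and the influence of self-selection are all unknown, so neither the size nor the net direction of bias can be derived. The matter should be settled before enrolment, because it concerns the study's only reference point.

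**What to change.** 1. Reconcile the Dissemination Plan with Sample Selection and Recruitment, Textbox 1 and the Recruitment paragraph. State that the primary and secondary analysis set consists of clinic-recruited dyads who meet Textbox 1, and that any other public users who consent form a separate cohort, reported descriptively only.
2. Extend the exclusion on development or testing to any prior use of NMS Assist, by patient or care partner, checked at enrolment against the account creation date in the system log.
3. Require the first Patient Activation Measure before the account is activated. The baseline visit offers an occasion for this.

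The cost is a few sentences of text, a log check for each dyad and a fixed order of steps at baseline. The real downside is the loss of any interested prior users from the main analysis. Their number is unknown and could slow recruitment if it is not small; the descriptive cohort keeps their usage and acceptability data.

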## Appendix

Multimedia Appendix 1 Standard Protocol Items: Recommendations for Interventional Trials checklist.

Multimedia Appendix 2 Peer-review report (stage 1) from the Parkinson’s UK - Grants for Non-Drug Approaches (London, UK).

Multimedia Appendix 3 Peer-review report (stage 2) from the Parkinson’s UK - Grants for Non-Drug Approaches (London, UK).

## Abbreviations

EQ-5D-5L: EuroQol 5 Dimension 5 Level
HCP: health care professional
MDS-NMS: Movement Disorder Society–Nonmotor Rating Scale
NASSS: nonadoption, abandonment, and challenges to the scale-up, spread, and sustainability
NHS: National Health Service
NMS: nonmotor symptoms
NMSQ: Nonmotor Symptoms Questionnaire
PDQ: Parkinson’s Disease Questionnaire
PPI: patient and public involvement
SPIRIT: Standard Protocol Items: Recommendations for Interventional Trials
WEMWBS: Warwick-Edinburgh Mental Wellbeing Scale
